## Methods/design

### Design overview

This research was approved (IRB #08-116) by the Committee on Human Research in the Behavioral Sciences in the Research Protections Office at the University of Vermont, the site where the work is being conducted. This is a concurrent two-arm study that randomizes individuals experiencing a current SAD-related depressive episode to 6 weeks of treatment with group cognitive-behavioral therapy (CBT) or light therapy (LT). The primary endpoint is depression recurrence in the next winter, testing for two-sided differences in depression recurrence in one treatment condition relative to the other in an intention-to-treat (ITT) analysis. The proposed trial goes beyond prior studies in four ways. (1) This study augments the generalizability of prior data by relaxing the inclusion/exclusion criteria to allow for comorbid diagnoses and stable antidepressant medication use and by demonstrating the feasibility of training experienced community therapists to facilitate the CBT groups. (2) Recurrences and potential intervening variables that could affect outcome (e.g., new treatments, summer remission status) are prospectively tracked in the interim between treatment endpoint and the following winter. (3) This study includes a second annual winter follow-up to obtain preliminary data on the comparative effects of CBT vs. LT two winters after the initial winter of study treatment. (4) The influence of potential modifiers on the effects of CBT vs. LT will be examined, including demographic variables, baseline depression severity, comorbidity, baseline antidepressant medication status, and complete or incomplete summer remission status.

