### Screening and enrollment

Given SAD’s inherent seasonal pattern, recruitment for this study begins each September and continues through mid-January. Individuals who respond to advertisements undergo a brief phone screening to assess inclusion/exclusion criteria. Respondents who do not endorse DSM-IV criteria for major depression, recurrent, with seasonal pattern and/or who satisfy any exclusion criterion on the phone screen receive a referral list. Respondents who appear to meet criteria on the phone screen are invited to review the informed consent document. We obtain informed consent before proceeding with any further study procedures. If they consent, the full Structured Clinical Interview for DSM-IV Axis I Disorders—Clinician Version (SCID-CV) is administered at an in-person screening visit. If a diagnosis of major depressive disorder, recurrent, with seasonal pattern is confirmed on the SCID and no axis I disorder requiring more immediate treatment is revealed, the Structured Interview Guide for the Hamilton Rating Scale for Depression—Seasonal Affective Disorder Version (SIGH-SAD) is administered to assess SIGH-SAD criteria for a current SAD episode. If SIGH-SAD criteria are not met, the individual is invited to attend SIGH-SAD interviews every other week. When a potential participant meets SIGH-SAD criteria for a current SAD episode, he or she is asked to attend a medical workup involving a routine physical examination and medical history to characterize the sample and assess the hypothyroidism exclusion. These evaluations are performed at the University of Vermont Clinical Research Center in the College of Medicine by a Physician’s Assistant. A nurse performs venipuncture to measure levels of TSH and thyroxine to screen for hypothyroidism. Individuals with laboratory results suggestive of hypothyroidism are excluded and referred for treatment. If the medical workup suggests normal thyroid functioning, the participant is asked to complete the pre-treatment assessment, at the conclusion of which he or she is randomized to a treatment group and enrolled in the study. At the end of January, SIGH-SADs are discontinued for any potential participant who did not meet the threshold for a SAD episode because of the low likelihood of developing a full threshold episode in that winter.

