### Treatments

#### Timing of the treatments

Participants enter the 6-week treatment phase on a continuous basis following randomization. The first week of February is the last treatment start date each fall/winter season of recruitment to ensure that all treatment is completed during the winter season and before spontaneous springtime remission typically occurs.

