### Formal follow-up assessments

Three formal, in-person follow-up assessments occur subsequent to study treatment completion: in the summer (i.e., the subsequent August), the next winter (i.e., January or February of the next wholly new winter season), and the second winter (i.e., January or February of the second wholly new winter season). All randomized participants are invited to attend follow-ups.

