### Outcome measures

#### Structured Interview Guide for the Hamilton Rating Scale for Depression—Seasonal Affective Disorder Version (SIGH-SAD)

The SIGH-SAD [34] includes the 21-item Structured Interview Guide for the Hamilton Rating Scale for Depression (HAM-D) and a supplementary 8-item subscale to assess atypical depressive symptoms associated with SAD. A trained rater, blind to the treatment condition, administers the SIGH-SAD at pre-treatment, treatment weeks 1–5, post-treatment, summer follow-up, next winter follow-up, and second winter follow-up. A second blinded rater subsequently rates audiotapes of the live SIGH-SADs to assess inter-rater reliability.

The primary outcome, depression recurrence status in the next winter, is defined according to the following SIGH-SAD criteria [35]: total SIGH-SAD score ≥ 20 + HAM-D score ≥ 10 + atypical score ≥ 5. The same criteria are used to define SAD episode onset (i.e., study inclusion criterion b) and depression recurrence status at follow-ups. Continuous depression scores and remission status on the SIGH-SAD represent secondary outcome measures. One or both of the following SIGH-SAD criteria are used to classify a full remission at post-treatment [36]: pre- to post-treatment reduction in total SIGH-SAD score ≥ 50% + HAM-D score ≤ 7 + atypical score < 7 OR HAM-D score ≤ 2 + atypical score ≤ 10. These remission criteria are also used to define remission status at the summer follow-up and annual winter follow-ups, except that the respective follow-up SIGH-SAD score, as opposed to the post-treatment score, is contrasted to baseline status.

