The above analysis will be repeated using the following alternate recurrence definitions as secondary outcomes: (1) meeting SIGH-SAD recurrence criteria at the prospective next winter follow-up OR depression recurrence defined as any major depressive episode as assessed by the LIFE OR fulfilling DSM-IV-TR major depression criteria in the interim between summer and next winter as assessed by the October and December tracking telephone calls, (2) a recurrence on the next winter SIGH-SAD OR depression recurrence status as assessed by considering any new treatment reported in the interim between treatment endpoint and next winter follow-up (except for ongoing LT for LT participants and using CBT skills on their own without a therapist for CBT participants) as prima facie evidence of recurrence, and (3) the most encompassing and conservative definition of recurrence that defines a recurrence as fulfilling criteria (1) OR (2) above.

Secondary analyses will examine how potential modifiers influence the effects of CBT and LT on the primary outcome of next winter recurrence on the SIGH-SAD. Potential modifiers will include: (1) demographic variables such as sex, age, and race (White vs. minority); (2) baseline characteristics such as pre-treatment depression scores, axis I comorbidity, and baseline antidepressant medication status; and (3) complete or incomplete summer remission status in the interim, as ascertained by the SIGH-SAD at the summer follow-up. This will be done using logistic and linear regression analyses for dichotomous and continuous outcomes, respectively, and including the modifiers as well as their interactions with treatment in the models. Although the models are essentially the same as those fitted to the complete data for the purpose of imputation, for this analysis they will be fitted to the imputed data sets, and the Rao-Blackwell estimates of the effects of the modifiers will be obtained [43].

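### Summer remission, an outcome measured after randomisation and treatment, is analysed as an effect modifier, so its interaction and within-stratum treatment effects can be biased

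*Protocol article*

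**What the plan says.** The Data analysis plan states the aim of this secondary work: "Secondary analyses will examine how potential modifiers influence the effects of CBT and LT on the primary outcome of next winter recurrence on the SIGH-SAD". It lists three groups of modifier: demographic variables, baseline characteristics, and "complete or incomplete summer remission status in the interim, as ascertained by the SIGH-SAD at the summer follow-up". One rule covers all three, namely logistic or linear regression "including the modifiers as well as their interactions with treatment in the models".

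Design overview gives the same list of modifiers. In the same paragraph it also counts summer status among the "potential intervening variables that could affect outcome (e.g., new treatments, summer remission status" that are followed between the end of treatment and the next winter.

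The SIGH-SAD section makes remission status on that scale a secondary outcome and adds: "These remission criteria are also used to define remission status at the summer follow-up and annual winter follow-ups". The article does not handle summer status differently from the baseline factors, and it does not warn that strata formed by it are not randomised groups.

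**The concern.** An effect modifier has a clear reading when it is fixed before randomisation: within each level, the two arms are still a randomised comparison. Summer status is not fixed then. It is observed after treatment and scored on a scale that the trial uses to measure treatment response. If CBT and LT act on it, or on what determines it, the CBT participants who remit in summer may differ in prognosis from the LT participants who remit, and likewise for those who do not.

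A difference between the two strata could then be read as moderation when it only reflects who ended up in each stratum. The trial could report that CBT works better in one kind of summer remitter, or that it has an effect within a stratum, when neither is true.

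**Working it through.** The plan gives no figure for this analysis, so there is none to reproduce. The check has three parts.

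**1. Timing and definition**

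- Randomisation (Screening and enrollment): at the end of the pre-treatment assessment, "he or she is randomized to a treatment group and enrolled in the study".
- Treatment (Timing of the treatments): "The first week of February is the last treatment start date each fall/winter season of recruitment". Six weeks from then ends in about mid-March.
- Summer assessment (Formal follow-up assessments): "in the summer (i.e., the subsequent August". That is about six months or more after randomisation and about five months or more after treatment ends.
- Possible routes from arm to summer status: LT participants may keep the light box through April (Light therapy section), and CBT teaches skills meant for use after the sessions end (CBT section).

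So the variable is post-randomisation, post-treatment and open to influence by arm.

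**2. What conditioning on it can do**

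These simulations are illustrative, because the documents give no summer remission rates. Let T be arm (1 = CBT, 0 = LT, allocated 1:1), U an unmeasured standard normal vulnerability, S summer remission and Y next-winter recurrence.

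- P(S = 1) = expit(a − c·U), where a and c may differ by arm.
- P(Y = 1) = 0.52 + τ·T + g·U, truncated to 0–1. Here 0.52 is the planning rate for LT, and τ is 0 or 0.29 − 0.52 = −0.23.
- S does not enter the equation for Y and τ is constant, so there is no true modification by S.
- Each scenario has 2 to 4 million subjects. RD is the risk difference, CBT minus LT. The interaction is RD in remitters minus RD in non-remitters, computed before rounding.

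| Scenario | Remission CBT/LT | RD overall | RD remitters | RD non-remitters | Interaction |
|---|---|---|---|---|---|
| No arm effect on S (c = 1.5, g = 0.12) | 0.67/0.67 | 0.000 | −0.001 | 0.001 | −0.001 |
| Arm shifts S, U does not affect S (c = 0) | 0.92/0.73 | 0.002 | 0.002 | 0.001 | 0.000 |
| Uniform shift, U affects S and Y (c = 1.5, g = 0.12), τ = 0 | 0.86/0.67 | 0.002 | 0.025 | 0.035 | −0.010 |
| Same, τ = −0.23 | 0.86/0.67 | −0.230 | −0.207 | −0.193 | −0.014 |
| c = 0.5 in CBT, 1.5 in LT (g = 0.12), τ = 0 | 0.72/0.69 | 0.000 | 0.025 | −0.049 | 0.074 |
| c = 0 in CBT, 1.5 in LT (g = 0.12), τ = 0 | 0.73/0.67 | 0.000 | 0.043 | −0.088 | 0.131 |
| Same, τ = −0.23 | 0.73/0.67 | −0.229 | −0.187 | −0.315 | 0.129 |
| c = 0 in CBT, 1.5 in LT (g = 0.20), τ = 0 | 0.73/0.67 | 0.000 | 0.071 | −0.144 | 0.214 |

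Across all runs in which c differed by arm, the interaction was 0.074 to 0.215. In two of the rows with a true null, overall remission was nearly equal by arm (0.72/0.69 and 0.73/0.67). Similar remission rates in the two arms therefore do not rule the problem out.

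A separate probit version had a true null and assumed remission of 76–89% under CBT and 67–70% under LT. It gave within-stratum differences of 0.016/0.028, 0.029/0.043, 0.030/0.058 and 0.054/0.088 (remitters/non-remitters). The contrasts between strata are therefore 1.2, 1.4, 2.8 and 3.4 points.

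If summer remission is instead a pure mediator, take P(S = 1) = expit(1 + shift·T) and P(Y = 1) = 0.72 − 0.18·T − 0.25·S. For shifts of 0.5 to 1.5 the overall effect is −0.202 to −0.228, and the effect adjusted for S is about −0.18. The mediated part has been removed.

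**3. Size against precision**

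Assume 80% remit, which gives 64 remitters and 16 non-remitters per arm, and a recurrence risk of 50%.

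- SE in non-remitters: √(2 × 0.25/16) = 0.177.
- SE in remitters: √(2 × 0.25/64) = 0.088.
- SE of the interaction: √(0.177² + 0.088²) = 0.198, about 20 points.

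A bias of 1.4 points is 0.014/0.198 = 0.07 standard errors, and 3.4 points is 0.17. A bias of 7.4 points is 0.37 standard errors, and 21.5 points is 1.09.

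**The case against.** The strongest reply is that the effect of arm on summer status may be negligible. The section on following all randomised participants says that people with SAD should, by definition, remit in summer. The section on treatment-endpoint differences reports pilot differences of under 2 points on continuous scores, with remission of 56% in LT and 46% in CBT. The simulated remission rates are assumptions, and most of the gaps favour CBT, opposite to those pilot figures. Under a uniform shift the spurious interaction is small beside a standard error of about 20 points. The larger values need the further assumption that the determinants of summer remission differ by arm. All of this stands as to size. It does not remove the flaw, because the plan itself expects some incomplete summer remission. The pilot also found opposite-signed correlations of baseline with next-winter scores in the two arms, so prognosis may act differently by arm.

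A second reply is that intervening may only mean occurring in the interval, and that the plan puts summer status in its own group, apart from baseline characteristics. That is fair: the label alone does not establish a mediating pathway. The point rests on timing, scoring and the common modelling rule.

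A third reply is that winter outcome by summer status is clinically informative, since the Background defines recurrence as a new episode after full remission. This also stands, and is why the analysis should be moved and relabelled rather than abandoned.

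**Conclusion.** The point holds in conditional form. The plan analyses a post-treatment outcome as a modifier by the rule used for baseline factors. If arm affects summer remission or its determinants, the interaction and the within-stratum effects in that secondary model can be biased. In the simulations the bias was nil without an arm effect and ranged up to about 22 points under the least favourable assumptions. The documents give nothing that would place this trial within that range.

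A reader might infer more, and the documents do not support it:

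- **That the estimates are biased.** With no arm effect on summer status or its determinants there is no bias.
- **That the treatment term and the baseline interactions are also distorted, or the model overloaded.** This needs all modifiers in one joint model, which the plan does not state.
- **That the interaction is attenuated because summer status is not named among the imputation predictors.** That list is of candidate predictors, the plan describes the modifier models as close to the imputation models, alternative imputation models are planned, and no attenuation was calculated.
- **That the main result is at risk.** The primary intention-to-treat comparison after multiple imputation does not condition on summer status.

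**What to change.** Restrict the modifier analysis to variables fixed before randomisation: the demographic and baseline factors already listed. Report summer remission by arm as an outcome. If winter recurrence by summer status is still wanted, put it in a separate exploratory analysis (mediation, principal stratum or purely descriptive), state its assumptions, and say that comparisons within summer strata are not randomised.

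This changes wording only. No data collection changes and the sample size stays at 160. The small downside is that the trial gives up a moderation claim for summer remission status.

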## Discussion

The study design was selected to answer the primary question: Do CBT and LT differ on depression recurrences during the subsequent winter season? The simple, straightforward CBT vs. LT design will answer that question and logically stems from pilot study findings. As a time-limited treatment, if CBT is associated with better outcomes than LT during the subsequent winter, CBT may represent a more practical, effective approach to long-term SAD management in clinical practice. The unique methodological challenges faced here likely generalize to designing intervention trials for other predictably recurrent and time-limited problems focused on long-term outcomes. Justification for the chosen design, consideration of alternative approaches, challenges faced with this population, and areas for future study are discussed below. Alternative designs would have required more patients, increased costs, and reduced power to detect a difference in the primary outcome.

### Rationale for not designing to detect differences between CBT and LT at treatment endpoint

The pilot study findings suggest that differences between CBT and LT following 6 weeks of treatment are quite small and that powering studies to detect these differences would not represent cost-effective use of resources. For example, 350 participants would be required in each treatment arm (*N* = 700) for a 2-group Χ^2^ test with a two-sided 0.05 significance level to achieve 80% power to detect the 10% difference in proportions remitted on the SIGH-SAD at post-treatment of 56% in LT vs. 46% in CBT (observed rates pooling across data from [name] et al., 2004, 2007). Moreover, the effect size associated with this 10% difference in remission is small, h = 0.20, and its meaning is not clear in terms of cost-benefit. Similarly, post-treatment differences between CBT and LT on continuous depression scores were consistently less than 2 points, a difference that is quite small and may not be clinically meaningful. The central public health challenge with regard to SAD is prevention of episode recurrence over subsequent winter seasons. Therefore, the current trial focuses on detecting a significant and clinically meaningful difference in the proportion of depressive episode recurrences between CBT and LT at the next winter follow-up if this difference exists.

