**Discussion:**

The chosen design answers the primary question of whether prior exposure to CBT is associated with a substantially lower likelihood of depression recurrence the next winter than LT. This design does not test the relative contributions of the cognitive-behavioral treatment components vs. nonspecific factors to CBT’s outcomes and is not adequately powered to test for differences or equivalence between cells at treatment endpoint. Alternative designs addressing these limitations would have required more patients, increased costs, and reduced power to detect a difference in the primary outcome.

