### Study aims

The primary aim is to compare the efficacy of CBT and LT on depression recurrence status, symptom severity, and remission status during the next winter season (i.e., the next wholly new winter season after the initial winter of treatment), which we argue to be the most important time point for evaluating clinical outcomes following SAD intervention. The hypothesis is that CBT will be associated with a smaller proportion of depression recurrences, less severe symptoms, and a higher proportion of remissions than LT in the next winter. The second aim is to compare the efficacy of CBT and LT on symptom severity and remission status at post-treatment (treatment endpoint). It is hypothesized that CBT and LT will not differ on post-treatment outcomes. An exploratory aim is to compare CBT and LT on recurrence, symptom severity, and remission two winters after treatment completion.

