### Sample size and statistical power

This RCT is designed to definitively test for a significant and clinically meaningful difference between CBT and LT on depressive episode recurrence during the next winter season (the primary endpoint). The true difference between CBT and LT (and the difference we observe in this more rigorous design) may be smaller than what was observed in the above pilot study. To determine sample size, the more conservative estimate of a 23% difference in recurrence was used, based on a worst case scenario assumption that all subjects who dropped out of the pilot studies at any time from randomization through the next winter follow-up would have evidenced a recurrence the next winter (52% in LT vs. 29% in CBT in the ITT sample). If the true difference is 23%, 80 participants per group (total *N* = 160) are required to provide 80% power to detect a significant difference in recurrence between CBT and LT with a 2-sided test and alpha = 0.05. With 80 participants per group, there is also 80% power to detect a 5-point difference in next winter continuous depression scores based on variance estimates from a worst-case scenario analysis of pilot data whereby pre-treatment scores were substituted for any missing next winter scores (14.3 ± 11.5 for CBT vs. 19.5 ± 11.5 for LT on the Structured Interview Guide for the Hamilton Rating Scale for Depression—Seasonal Affective Disorder Version).

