### Rationale for not designing to establish equivalence between CBT and LT the next winter

The motivation for this trial is based on pilot data showing that depression recurrence in the next winter season may be substantially lower with CBT than with LT [11]. Therefore, it is more important to test whether depression recurrence in the subsequent winter is lower in one treatment relative to the other than to test for equivalence between CBT and LT. If CBT and LT are “equivalent” (i.e., the true difference between the therapies is functionally equivalent to zero, indicating the absence of a difference between the treatments), it would require 280 subjects in each cell (*N* = 560) to test if recurrence rates are equivalent within 10% (i.e., LT-CBT > −0.10). An equivalence study of this size is not feasible or warranted in light of the pilot data. Furthermore, a reduction of recurrence would be the most, if not the only, compelling reason for widespread adoption of CBT in clinical practice because the vast majority of practitioners and researchers who specialize in SAD have a chronobiological orientation and enthusiasm for LT.

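### The sample size quoted for the post-treatment comparison should be 392 per arm, not 350, and Aim 2 predicts a null result that the trial, by its own account, is not powered to test (minor)

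*Protocol article*

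**What the plan says.** The protocol article's section on the rationale for not designing to detect differences at treatment endpoint gives a worked example. The pooled pilot remission rates are "56% in LT vs. 46% in CBT". The method is a two-group chi-square "test with a two-sided 0.05 significance level to achieve 80% power". The result is that "350 participants would be required in each treatment arm", N = 700 in total. The same paragraph adds that "the effect size associated with this 10% difference in remission is small, h = 0.20".

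The section on study aims makes the post-treatment comparison of symptom severity and remission the second aim, and states: "It is hypothesized that CBT and LT will not differ on post-treatment outcomes". The discussion part of the abstract says that the design "is not adequately powered to test for differences or equivalence between cells at treatment endpoint". The sample size section sets 80 per group, from next-winter recurrence of 52% vs 29%.

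**The concern.** There are two separate issues, and neither depends on the other.

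First, the worked example states every input, so a reader can check it, and 350 does not follow from those inputs. It also disagrees with the effect size in the next sentence.

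Second, Aim 2 predicts a null. An underpowered comparison tends to come out non-significant whether or not the prediction is true, so the likely result would look like confirmation. At stake is how a non-significant endpoint result is read. It could be taken to show that CBT matches the established acute treatment, when the data would be compatible with a sizeable advantage for either arm.

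**Working it through.** **Inputs.** From the endpoint rationale section: p1 = 0.56 (LT), p2 = 0.46 (CBT), difference 0.10, mean 0.51, two-sided alpha 0.05 (z = 1.960), power 80% (z = 0.8416), h = 0.20, stated n = 350 per arm. From the sample size section: 80 per arm. Allocation is 1:1.

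**Step 1: try to reproduce 350.** The chi-square sample size per arm is

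n = [1.960 × √(2 × 0.51 × 0.49) + 0.8416 × √(0.56 × 0.44 + 0.46 × 0.54)]² / 0.10²

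= [1.960 × √0.4998 + 0.8416 × √0.4948]² / 0.01 = (1.3856 + 0.5920)² / 0.01 = 391.1, so **392 per arm, N = 784**.

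Other conventions:

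| Method | n per arm |
|---|---|
| Chi-square, pooled variance under the null | 392 |
| Chi-square with continuity correction | 411 |
| Unpooled variance | 389 |
| Arcsine, computed h = 0.2004 | 391 |
| Arcsine, h = 0.20 exactly | 393 |
| One-sided | 308 |
| One-sided with continuity correction | 328 |

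None gives 350. The primary sample size of 80 per arm is close to the continuity-corrected result for 52% vs 29% (79; uncorrected 71). The same convention here would give 411, which is further from 350.

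**Step 2: power at 350 per arm.** [0.10 − 1.960 × √(0.4998/350)] / √(0.4948/350) = (0.10 − 0.0741) / 0.0376 = 0.690, which corresponds to **75.5%** (exact enumeration of the uncorrected test: 76.5%). Quoted N against required N: 700/784 = 0.89, about 11% too low.

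**Step 3: check against the printed h.** h = 2·arcsin√0.56 − 2·arcsin√0.46 = 0.2004, so the printed 0.20 is right. It implies 2 × (1.960 + 0.8416)² / 0.2004² = 391 per arm. For 350 to be right, h would have to be √(2 × 7.849 / 350) = 0.212.

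**Step 4: could rounding of the rates explain it?** Unrounded rates compatible with 56% and 46% give anything from about 324 to about 483 per arm, so 350 is reachable if the true gap was about 10.5 to 10.6 points (355 to 348 per arm). That gap has h near 0.21. Any h that rounds to 0.20 is below 0.205 and needs at least 2 × 7.849 / 0.205² = 373.5, so 374 per arm. The printed rates, h and n cannot all be right, and the rates and h agree with each other.

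**Step 5: what 80 per arm can say about Aim 2 remission.**

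- Power for 56% vs 46%: [0.10 − 1.960 × √(0.4998/80)] / √(0.4948/80) = (0.10 − 0.1549) / 0.0786 = −0.698, which corresponds to **24.2%** (exact enumeration 23.8%; about 19% with continuity correction).
- Chance of a non-significant result if LT really is 10 points better: 100 − 24.2 = 75.8%, about three times in four.
- Half-width of the 95% interval: 1.960 × √(0.4948/80) = 0.154, about **±15 points**.
- Difference detectable with 80% power: about 22 points.

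**The case against.** The strongest reply concerns consequence. The 350 is introduced as an example of why the endpoint comparison was not powered. The trial's size comes from next-winter recurrence and does not use it, and 392 makes the authors' case stronger. All of that stands. A reader might infer from the error that the trial itself is wrongly sized, and the document does not support that.

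The second reply is that the low power is openly declared. The abstract says so, and a whole section explains the choice. This also stands, and a reader who concluded that the limitation is concealed would be wrong. The 24% puts a number on something the authors already concede. What the disclosure does not do is remove the tension with a stated hypothesis of no difference.

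Third, nothing in the article says that a non-significant endpoint result will be claimed as equivalence, and endpoint reporting may be set out in a full protocol or analysis plan that is not shown. That is fair. The point is therefore about the wording of the aim as printed, not about a planned false claim.

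Finally, a reader might want to judge Aim 2 against the 10-point figure in the section on equivalence the next winter, where the aim would be "to test if recurrence rates are equivalent within 10" percent. The document does not support that use. The figure belongs to next-winter recurrence, in a design the authors rejected, and is written as a one-sided bound. No margin is set for post-treatment remission, so no rule for declaring comparability can be taken from the article.

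**Conclusion.** The point holds, and it is minor. The quoted 350 per arm (N = 700) is wrong as printed. The stated inputs require 392 per arm (N = 784), or about 411 per arm with continuity correction, and 350 gives about 75% power. The primary comparison and the trial's size are unaffected.

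Aim 2's no-difference hypothesis does not fit the article's own statement about power at treatment endpoint. With about 24% power against the pilot gap and an interval of about ±15 points, a non-significant remission result cannot support it.

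The 24% and ±15 points assume that the pilot rates are true and that all 80 per arm contribute post-treatment data; missing data would make both worse. They concern SIGH-SAD remission only. The article gives no post-treatment standard deviation, so no matching figure is offered for the continuous scores.

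**What to change.** In the endpoint rationale section, replace 350 per arm (N = 700) with 392 per arm (N = 784), or keep 350 and state that it gives about 75% power. If a continuity-corrected test was intended, say so and give 411.

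In the study aims, reword Aim 2 as estimation: the post-treatment difference between CBT and LT will be reported with its 95% interval, and a non-significant result will be treated as inconclusive and not as evidence of comparability. The pilot-based expectation of a small difference can stay as background. Do not add a comparability threshold borrowed from the next-winter equivalence section.

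The cost is wording only: no more participants, assessments or analyses.
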